# Methods

## Study Design

A randomised field experiment will be used to provide information on the efficacy of the DPT vaccination to mothers with young children. Families will be individually randomised into three study arms. Mothers in the first treatment group will receive the information framed in positive terms. A second treatment group will provide essentially the same information on efficacy but framed in negative terms. The third arm acts as a control group with no information given to the mother. Randomisation will done using the digital equivalent of a three-sided coin. Enumerators will be blind to the assignment of the intervention.

Information will be given to mothers in the privacy of their own home. Nevertheless, randomisation at the individual household level gives rise to concerns of potential contamination. A household given one of the two information interventions may then interact and share information with the households in the control group. The extent to which information spills over to other neighbours and peers of treated households will be estimated in the standard way, as explained in Section 4.6, by exploiting random variation in the geographical density of households.

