## Analysis

The primary analysis will compare the proportion of children with three doses of DPT in the two treatment groups pooled together against the control group. A logistic regression with a dummy variable representing the two treatment groups combined will produce risk ratios with 95% confidence intervals adjusted for the distance stratifying variable (included as two dummy variables), with the control group as the omitted reference category. Fully adjusted risk ratios will also be generated with the inclusion of baseline characteristics. Secondary outcomes will be analysed in a similar manner, but using OLS in the case of continuous outcomes.

Several additional analyses will be conducted. First, an analysis to identify the effects of the two variants of the intervention will be conducted in a treatment group analysis. Each of the three groups will be compared against each other. The comparison between the two information groups will identify whether framing matters. Second, an analysis of information spillovers will be conducted by exploiting random variation in the geographical density of households assigned the treatment groups ([Dupas, 2014](#_ENREF_5), [Kremer and Miguel, 2007](#_ENREF_12), [Miguel and Kremer, 2004](#_ENREF_19)). Information on the geographical coordinates of households will be used to generate a variable that indicates for each household the share of other households within a given radius who received the information intervention. The presence of information spillovers is examined by the inclusion of this density variable. The sensitivity of the results to different radii will be explored (ie. 250 metres, 500 metres, 750 metres). Third, differences in the primary endpoint across specified subgroups will be assessed by adding a treatment-by-subgroup interaction terms to the binary regression models. This will be done separately for the following subgroups measured at baseline: 1) index of the mother’s perception of the efficacy of tetanus vaccination; 2) gender of the child; 3) household wealth; 4) education level of the mother; and 5) distance to the nearest government facility. In the analysis of secondary outcomes, OLS will be used in the case of continuous outcomes.

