## Informed Consent

Informed consent will be required from mothers before: 1) administering the household survey; and 2) delivering the information intervention. For each of three consent processes, an information form will be read and given to participants on the purpose of the study, the risks and benefits of the study, the broad content of the interview, the confidentiality of the data, the voluntary nature of the interview, the possibility of stopping the study or interview at any time without reason, and the contact details of the principal investigators. Consent from women indicated by a thumb print, with written confirmation by the enumerator of such consent being given, will be sought and must be given prior to the information intervention being delivered or the interview commencing.

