# Appendix

## Updates to the original study protocol

A number of changes were made to the original study protocol (dated 3rd December 2014) before the baseline household survey and the delivery of the information intervention. These changes are reflected in both this version of the study protocol and the online trial registration for the study. The changes and the justification for the changes were as follows:

- Eligible mothers were randomly assigned in a ratio of 1:1:1 to one of three study arms using simple randomisation. In the original study protocol it stated that randomisation would be stratified according to distance of the residence to the nearest public health facility. We did not collect data on distance to the nearest public health facility because we felt such information would be unreliable.
- Potentially eligible participants were identified through two channels: a household survey conducted by the research team nine months prior to the study and a list of mothers who had given birth in the past year provided by the community health worker (known as ASHAs) in each village. In the original study protocol it stated that all participants would be identified through the first channel only. After collecting data from the household survey conducted nine months prior to the start of the study, it became clear the sample sizes obtainable from this method would be insufficient. Hence, the second channel of identifying eligible participants was also used.
- One criteria for inclusion in the study was that the child should be aged 0-36 months. In the original study protocol the age range was 0-11 months. Revisions to the study protocol recognised that older children should be eligible because they can receive catch-up vaccinations for DPT.
- In the original study protocol we envisaged collecting data on general health care seeking behaviour of members in the participating households using a family health pictorial diary. This data collection method was dropped altogether.

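### The spillover exposure is justified by neighbours assigned to information but built from neighbours who received it, and only the assigned share is guaranteed random

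*Protocol*

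**What the plan says.** The Protocol randomises by family (Study Design): "Families will be individually randomised into three study arms". The appendix on updates confirms simple randomisation: "Eligible mothers were randomly assigned in a ratio of 1:1:1 to one of three study arms using simple randomisation". Two in three study households are therefore expected to be assigned to information, wherever they live.

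Study Design recognises that treated and control households may talk to each other, and says that spillover will be estimated "by exploiting random variation in the geographical density of households". Analysis gives the detail in adjacent sentences. The source of identification is stated as "exploiting random variation in the geographical density of households assigned the treatment groups". The variable to be generated is the "share of other households within a given radius who received the information intervention", with 250, 500 and 750 metres to be explored as radii. Its coefficient is the test: "The presence of information spillovers is examined by the inclusion of this density variable".

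Informed Consent asks for consent to the survey and, as a separate item, to delivery of the information. Consent "must be given prior to the information intervention being delivered". Participants and Inclusion Criteria also makes consent to the study a condition of entry. The document gives no expected rate of non-receipt. It does not say whether consent to delivery comes before or after randomisation, or whether the other households in the radius are study households or all households.

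**The concern.** Two adjacent sentences define one regressor in two ways. A share of assigned neighbours is fixed by the randomisation and cannot depend on what kind of village it is. A share of receiving neighbours is an as-treated exposure: it combines the random allocation with the neighbours' willingness to accept the visit. If that willingness is lower in villages where vaccination is also lower, the received share carries village differences into the spillover coefficient.

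What is at stake is the reading of the trial. A false spillover signal would lead readers to think that the control group had been contaminated and that the main effect was diluted.

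**Working it through.** **1. The plan's own figure.** None is given for the spillover analysis. Table 3 serves only to set the scale. For 10% against 17% with allocation 1:2, the pooled proportion is (0.10 + 2 × 0.17)/3 = 0.1467, and

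n(control) = [1.96·√(1.5 × 0.1467 × 0.8533) + 0.8416·√(0.10 × 0.90 + 0.17 × 0.83/2)]² / 0.07² = (0.8492 + 0.3372)² / 0.0049 = 287.3.

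This rounds up to 288, with 576 in the pooled arms, as printed: 864 in all.

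**2. Expected exposure.** Let r be the receipt rate among assigned households in an area. The expected assigned share is 2/3 in every area. The expected received share is (2/3)·r, which moves with r.

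**3. Mechanism by hand, with no true spillover.** Take two equally common kinds of area, with control uptake of 15% and 5% (assumed), and 4 other study households in reach (5 per area). Ignoring own arm, the slope on the share is about Cov(share, uptake) / Var(share).

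- Receipt 100% and 70%: shares 0.667 and 0.467. Cov = 0.10 × 0.05 = 0.005. Var = 0.10² + (0.2222 + 0.2489)/(2 × 4) = 0.0100 + 0.0589 = 0.0689. Slope = 0.005/0.0689 = +0.073.
- Receipt 100% and 96%: shares 0.667 and 0.640. Cov = 0.0133 × 0.05 = 0.00067. Var = 0.0002 + 0.0566 = 0.0568. Slope = +0.012.
- Receipt 85% in both: shares equal, Cov = 0, slope 0.
- Assigned share: 0.667 in both, Cov = 0, slope 0.

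The slope is for a share going from 0 to 1. In the first, deliberately unfavourable case, one SD of the share is √0.0689 = 0.26, which is worth 0.26 × 0.073 = 0.019, or about 2 points.

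**4. False-positive rate.** Simulation with no true spillover: 900 households, 2/3 assigned, base uptake 15%, direct effect 7 points, and area SD of uptake 0.7 on the logit scale. The outcome is regressed linearly on own assignment and the leave-one-out area share, with cluster-robust standard errors, a two-sided 5% test and 1,500 runs. Receipt has an area SD of 1.0 on the logit scale. The layout of 180 areas × 5 takes its 180 from the earlier household survey (Identification of participants); the number of study villages is not stated, so 90 × 10 is shown too. Entries are rejection rates (%) for the received share at correlation 0 / 0.5 / 0.9 between area receipt and area uptake.

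| Receipt in a typical area | 180 × 5 | 90 × 10 |
| --- | --- | --- |
| 98% | 5.9 / 7.2 / 7.3 | 6.1 / 7.7 / 10.7 |
| 90% | 5.5 / 14.4 / 29.8 | 6.5 / 24.7 / 51.5 |
| 80% | 6.5 / 28.7 / 63.7 | 7.5 / 42.3 / 80.7 |

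The assigned share gave about 5-7% throughout, with a mean coefficient of about 0. At 90% receipt and correlation 0.5, the received share's mean coefficient was +0.05 (180 × 5) or +0.11 (90 × 10).

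The receipt rates in the table are those of the median area. Averaged over areas they are lower: for example, the mean of 1/(1 + exp(−(ln 9 + u))) with u standard normal is 0.87. Rerunning 180 × 5 with the average itself set to 90% gave 11% and 22% at correlations 0.5 and 0.9. A separate simulation of 180 × 5 gave 4 / 11 / 31% at 90% receipt and 7 / 26 / 47% at 80%, with 4-7% for the assigned share. Hence the summary of roughly 11-31% at 90% receipt.

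**5. Denominator.** Suppose the share is taken over all households in the radius (100 assumed), and areas with more eligible, under-vaccinated families have lower uptake. Then even the assigned share carries the local density of eligible families. In 1,000 runs, its false-positive rate was 8% / 37% / 85% at correlation 0 / 0.3 / 0.6, and 6-7% once the eligible share was in the model.

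**The case against.** The best defence is that *received* is loose wording. Analysis states the random-assignment rationale first, Study Design uses the same verb for membership of an arm, and nothing says that receipt will be recorded separately from allocation. Non-receipt may also be rare. Study consent is an entry criterion, and a mother who withdraws after the home session has still received the information. No passage suggests that receipt varies between villages. All of this stands as a limit on size. It does not defend the definition, because the sentence that fixes the variable names receipt, and a separate consent to delivery gives receipt a route to differ from assignment.

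A reader might infer more than the documents support:

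- That the regressor is certainly non-random. The bias needs non-receipt that is material, clustered by area and related to uptake. With full receipt the two definitions coincide.
- That this analysis is the only protection against contamination. Study Design also relies on delivery in the privacy of the home.
- That the main result is biased. The spillover model is an additional analysis.
- That a fixed number of points of bias can be quoted. The inputs that drive it, the receipt rate, its spread between areas and its correlation with uptake, are not in the document.

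**Conclusion.** The inconsistency is real and the concern holds conditionally. Analysis claims identification from random assignment and then specifies an exposure that is not guaranteed random. With nearly complete receipt, or non-receipt unrelated to uptake, the test stays close to its nominal level: about 5-7% with 180 areas of 5, and at most about 11% with 90 areas of 10. At 90% receipt with a correlation of 0.5-0.9 it is roughly 11-31% with 180 areas, and higher with fewer, larger areas. The assigned share avoids this in every scenario, provided the denominator is limited to randomised study households. These rates rest on assumed receipt, area variation and correlation, and on a linear model with areas standing in for radii. The primary comparison of pooled information arms with control is untouched. The wording should be corrected, because the correction costs almost nothing and removes the dependence on these unknowns.

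**What to change.** In Analysis, define the exposure for each of the three radii as the number of other randomised study households within the radius that were assigned to either information arm, divided by the number of other randomised study households within that radius. Take assignment from the allocation list. Changing *received* to *assigned* is not enough if the denominator could be read as all households. If that denominator is wanted, the local share of eligible households must be in the model. A receipt-based share may be shown only as a sensitivity analysis. If the analysis has already been run, the report should say which list the share was built from.

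The cost is a sentence or two. Allocation and household coordinates are already part of the planned data, so nothing new has to be collected. The downside is slight dilution of a true spillover if some assigned households were not reached.

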### Identification of participants

Potentially eligible participants were identified through two channels. First, a household survey conducted by the research team for a different purpose nine months prior to the study will be useful in identifying eligible women to participate. The household survey will use the sampling frame provided by the most recent census, conducted in 2011. The sampling is based on a two-stage design. The first stage involves the selection of 180 primary sampling units or clusters using systematic sampling proportional to size. The second stage involves a full household listing on entry to the cluster to create the sampling frame of eligible women (i.e. gave birth in previous two years). From this sampling frame 20 eligible women per cluster will be selected at random and invited for interview. Second, a list of mothers who have given birth in the past year provided by the community health worker (known as ASHAs) in each village will also identify eligible women to participate. Study researchers will visit the household of each potentially eligible mother, assess eligibility based on either vaccination cards or self-reports, and seek informed consent.

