## Data Management

An important ethical risk of the study pertains to breaches of confidentiality. The study will make every effort to minimise the risk of breaches of confidentiality, particularly in relation to data management and the linking of datasets. The research intends to link data from different sources. The linking of data with geographical identifiers elevates the importance of maintaining confidentiality.

A number of steps will be taken in terms of management of the data. First, data using the various data collection tools will be entered by enumerators at the time of interview and will be linked only by the PIs for the purposes of random assignment and analysis. In this way, misuse or breach of confidentiality at the data entry level will be reduced by a great extent. Second, data will be stored electronically (no paper questionnaires are to be used) in London (at LSHTM) and Delhi (at Sambodhi) and will only be accessed by the PIs and other members of the research team. No other persons will have access to the securely kept data.

Third, the datasets will contain no information that would allow identification of any individual woman or household. They will contain no information on names or GPS information. The village cluster will be coded such that it is not possible to know the name of the village from the datasets. GPS information on households will be collected using a separate data collection form, entered into digital format separately and the digital format of the data will be stored in its own data file. Datasets will not be linked to the GPS information dataset, except by the PIs at the time of analysis. The variables containing the GPS information will otherwise be scrambled such there is an uncertainty in the location of observation of at least 10 kilometres.

Fourth, as is common practice, data will be reported in aggregate format only (eg. means, subgroup means, percentages, regression outputs) such that no individual is identified. Finally, at the end of the project the data will be made available to researchers under conditions of restricted access. The data can only be used for research or teaching purposes. Access the data will be granted by the PIs on an individual basis in response to requests made using a form. The data will not contain any identifiers or names that would allow identification of an individual. The platform to make the data available to researchers will be the LSHTM data repository.

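### The spillover test uses a neighbour-share regressor that village neighbours largely have in common, but the protocol makes no allowance for village correlation; default standard errors would make it anti-conservative

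*Protocol*

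**What the plan says.** Study Design states "Families will be individually randomised into three study arms", acknowledges that informed mothers may pass the information to control households, and refers the reader to Section 4.6 for how spillover will be estimated. That section (Analysis) defines a variable for each household as "the share of other households within a given radius who received the information intervention". It then says "The presence of information spillovers is examined by the inclusion of this density variable", with radii of 250, 500 and 750 m as a sensitivity analysis. This sits under the sentence "Several additional analyses will be conducted", so it is not the primary analysis.

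The base model in the same section is: "A logistic regression with a dummy variable representing the two treatment groups combined will produce risk ratios with 95% confidence intervals". OLS is named for continuous outcomes. No variance estimator is named for the density coefficient, and no cluster, random-effect, spatial or randomisation-based method appears elsewhere in the protocol.

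The participants nevertheless come from clusters. Under Identification of participants, the source survey is described as: "The first stage involves the selection of 180 primary sampling units or clusters using systematic sampling proportional to size". A second channel uses the village health workers' lists. Data Management shows that a village identifier is kept: "The village cluster will be coded such that it is not possible to know the name of the village from the datasets".

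**The concern.** Individual randomisation makes a mother's own assignment independent of her neighbours' assignments, so ordinary standard errors serve for the treatment contrast even if uptake is correlated within villages. That protection does not extend to the density variable. Two participants in one village count nearly the same set of other participants, so their density values are close to each other by construction. The density coefficient is estimated largely from differences between villages, and default standard errors credit it with more independent information than it has.

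Uptake is plausibly correlated within a village, since mothers share a health worker and probably local services. In that case the confidence interval would be too narrow and the test would signal spillover too often. Because the protocol relies on this analysis to address contamination, a false signal could colour the reading of the main result, for example by putting a small difference down to leakage of information into the control arm.

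**Working it through.** **Inputs.** Allocation 1:1:1 by simple randomisation (appendix, Updates to the original study protocol), so 2/3 of families are informed. Total N = 288 + 576 = 864, from the 7-point pooled cell of Table 3 at 10% control uptake. The one cluster count in the protocol is the 180 units of the source survey. The ICC and the number of villages contributing participants are not given; they are assumptions here, taken as 0.05 to 0.20 and as 180, 90 or 60.

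**The plan's own figures.** The protocol gives none for the spillover test. Table 3 is the only calculation available to check. The two-proportion formula with pooled variance, two-sided 5%, 80% power and no continuity correction reproduces all 12 single-arm sizes (for example 295 and 240 for 8 and 9 points at 10%) and all 12 control-group sizes in the pooled part (for example 288 for 7 points). Those sizes assume individual randomisation with no design effect.

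**Step 1: correlation of the regressor.** Take a village with *m* participants, all within the radius, each informed with probability *p*. The share for mother *i* is the number informed among the other *m* − 1, divided by *m* − 1. Its variance is p(1−p)/(m−1). Two mothers have *m* − 2 others in common, so the covariance of their shares is (m−2)p(1−p)/(m−1)². The correlation is therefore (m−2)/(m−1):

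- 180 villages: m = 864/180 = 4.8; 2.8/3.8 = 0.74
- 90 villages: m = 9.6; 7.6/8.6 = 0.88
- 60 villages: m = 14.4; 12.4/13.4 = 0.93

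For own assignment the corresponding correlation is 0.

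**Step 2: variance inflation.** 1 + (m−1) × [(m−2)/(m−1)] × ICC = 1 + (m−2) × ICC. For own assignment it is 1.

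**Step 3: true size of a nominal 5% test with default standard errors.** 2 × [1 − Φ(1.96/√inflation)]. With 180 villages and ICC 0.05, the inflation is 1 + 2.8 × 0.05 = 1.14 and the size is 6.6%.

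| Villages | ICC | Inflation | Formula | Simulated |
|---|---|---|---|---|
| 180 | 0.05 | 1.14 | 6.6% | 6.2–6.8% |
| 180 | 0.10 | 1.28 | 8.3% | 7.2–8.8% |
| 180 | 0.20 | 1.56 | 11.7% | 9.7–12.9% |
| 90 | 0.05 | 1.38 | 9.5% | 8.3–9.8% |
| 90 | 0.10 | 1.76 | 14.0% | 10.5–14.7% |
| 90 | 0.20 | 2.52 | 21.7% | 17.4–21.1% |
| 60 | 0.05 | 1.62 | 12.4% | 10.2–12.2% |
| 60 | 0.10 | 2.24 | 19.0% | 15.2–19.6% |
| 60 | 0.20 | 3.48 | 29.3% | 23.1–29.1% |

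The last column spans two sets of simulated trials with 864 mothers and no true spillover (6,000 and 3,000 runs per setting, linear model with own assignment and density). The formula applies the stated ICC to all mothers; if the village effect is weaker among informed mothers, the inflation is smaller. At ICC 0 the size is 5%.

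**Step 4: checks on the remedy and on the primary contrast.** With village-clustered standard errors the same simulations rejected in 5.3 to 7.0% of trials. A further logistic simulation with 720 mothers and 1,500 runs gave 6 to 9% with clustered errors at 60 villages, so a small-sample correction is needed when villages are few. In that simulation the own-assignment test with ordinary standard errors stayed at 3.9 to 5.5%.

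**Limit of the calculation.** It places the whole village inside the radius. At a radius smaller than the village, neighbours share fewer counted households, so the regressor correlation and the inflation both fall.

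**The case against.** The strongest objection is that the fault is read from silence. The protocol never says that mothers will be treated as independent, and a logistic or OLS model is compatible with clustered standard errors. The estimator for an additional analysis could sit in a statistical analysis plan that is not at hand, and the protocol cites published studies for the method whose handling of standard errors cannot be seen here. This stands in part: a reader might infer that the protocol has chosen an independence-based test and will over-declare spillover, and the text does not support that as fact. What remains is that Study Design names the Analysis section as the place where the method is explained, and that section gives the regressor, the way it is tested and the radii without any allowance for villages. The appendix on deviations also justifies simple statistics for the intervention effect by the use of simple randomisation. That argument is sound for own assignment and does not carry over to the density term.

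A second objection is that the larger error rates need 60 to 90 villages, which no section documents. At 180 villages and ICC up to 0.10 the excess is modest. That is fair. But 180 describes the source survey, not the trial sample. The appendix says this channel yielded too few participants and was supplemented from village lists, so the number of contributing villages is open in either direction.

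A third is that village clustering is not the only reasonable choice, since a radius can cross a village boundary. That is also fair, and randomisation inference is an alternative.

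A reader might also infer that the main result is compromised. It is not: the own-assignment contrast keeps its size.

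**Conclusion.** The point holds in conditional form. The protocol makes no allowance for village correlation in a test whose regressor is largely common to neighbours. If the default standard errors of the named models are used, and uptake is positively correlated within villages, the test is anti-conservative and its interval too narrow. For ICC 0.05 to 0.20 the false-positive rate is roughly 6 to 12% with 180 villages and roughly 10 to 30% with 60 to 90. These figures assume 864 mothers spread evenly over the villages and a radius that covers the village; a smaller radius gives less. The mechanism is firm, while the size is uncertain because neither the ICC nor the number of contributing villages is documented. Only the spillover coefficient in an additional analysis is affected. It still merits correction, because that analysis is the protocol's stated response to contamination.

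**What to change.** Add to Analysis: every model containing the density variable, at each of 250, 500 and 750 m, uses standard errors clustered on the coded village cluster already held, with a small-sample correction if few villages contribute. Alternatively, specify randomisation inference that re-draws the assignments under the 1:1:1 scheme and recomputes the density each time; this also copes with radii that cross village boundaries. Report the number of villages contributing and the number of participants per village. If the density models have already been fitted, re-running them with the stated estimator is enough. The primary contrast needs no change. The cost is one sentence and one software option, or modest computing time for re-randomisation. The drawback is a wider spillover confidence interval, so a null spillover result would be less informative.
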